### Informed consent

The researchers will screen and record the medical history of participants and obtain written informed consent from the recruited participants with a detailed explanation. On the informed consent form, the recruited subjects will be asked whether they agree to share their data and donate their breast milk, cord blood, and feces.

### Interventions

#### Intervention strategy

The *L. reuteri* strain used in this study is a probiotic supplement derived from breast milk and formulated in the form of a solid beverage with highly acceptable properties. The solid beverage contained fructooligosaccharides, erythritol, stachyose, resistant dextrin, strawberry juice powder, and vitamin C. The products of the solid beverages with and without *L. reuteri* have the same taste and are packed at 1.5 g per package. *Limosilactobacillus reuteri* has been reported to colonize the intestines of almost all vertebrates and mammals, has good biocompatibility, and is widely used for food production. We previously used targeted sIgA immunomagnetic bead enrichment and separation technology (patent number ZL201610975479. X) to isolate a strain of sIgA-coated *L. reuteri* FN041 (patent strain storage number: GDMCC60546) from Gannan breast milk. This species is included in the list of bacterium strains that can be used for food released by the National Health Commission and is a probiotic that can be used in ordinary food. Genome sequencing analysis revealed that *L. reuteri* FN041 has no horizontally transmissible antibiotic resistance or pathogenic genes.

The selected doses (1 × 10^9^, 5 × 10^9^, and 1 × 10^10^ CFU/d) of *L. reuteri* FN041 in the first stage are in the reported safe range and the optimal dosage will be determined and subsequently applied in the second stage. The World Allergy Organization recommends probiotic administration to pregnant females at high risk of bearing a child with allergy during pregnancy and, in case of breastfeeding, lactation (Fiocchi et al., 2015). Therefore, oral intervention with the respective solid drinks for the recruited subjects in the two stages will start from the gestational age of 32–36 weeks until delivery. The mothers will continue to consume the corresponding solid drinks daily for 6 months, from 1 to 3 days after delivery, during the lactation period. All the solid drinks are suggested to be taken orally at bedtime once daily.

#### Criteria for discontinuing or modifying allocated interventions

Participants will be allowed to withdraw from the research at any time without consequences.

#### Strategies to improve adherence to interventions

The project team comprises pediatricians, dermatologists, pediatric nurses, and clinical researchers. This study will ensure that the health or interests of the research subjects are not harmed. We will acknowledge the support of research participants to gain active cooperation. At the beginning of the project, technical training will be provided to the researchers, and specific researchers will regularly contact the subjects to record data. Researchers will regularly follow up, promptly inquire, and collect information on changes in the physical condition of pregnant females and infants and ensure the consumption of probiotics. A mobile app will be developed to strengthen the interaction between researchers and subjects. Participants who fail to complete the entire experimental process will be inquired about their reasons. To ensure the reliability of the results, every effort should be made to keep the number of dropouts below 10%; otherwise, additional research will have to be conducted.

#### Relevant concomitant care permitted or prohibited during the trial

During the research period, neither mothers nor infants will use any probiotic products other than those used in this experiment. Mothers will be encouraged to breastfeed their infants and will be provided with the necessary medical guidance.

#### Allocation and blinding

The participants recruited in this study will be grouped randomly in the first stage of project implementation so that they are consistent with each group according to their age, economic situation, educational level, and other influencing factors.

In the first stage, both the on-site and laboratory analyses will be conducted using a double-blind method. The samples of *L. reuteri* and placebo used in the experiment will be processed and produced by a third-party company. The project organizer, researchers, and participants will not be informed about the intervention methods they receive. The biological samples analyzed by laboratory technicians (including blood, breast milk, and feces) will be blinded to their specific sources and grouping situations until the end of all experiments.

In the second stage, a multicenter cohort study will be conducted, in which the recruited subjects will not be blinded because this stage has been designed to explore the efficacy of maternal intervention with *L. reuteri* in preventing infantile AD.

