### Trial design

The study is divided into two stages. In the first stage, a multicenter, randomized, double-blind, placebo-controlled intervention study will be conducted in 340 pregnant females with babies at high risk for AD recruited from the Wuxi Maternity and Child Health Care Hospital affiliated with Jiangnan University and the Affiliated Hospital of Qingdao University. These subjects will be randomly divided into four groups (*n* = 85 for each group): (1) placebo group administered with the carrier solid beverage daily, (2) group administered with *L. reuteri* FN041 solid beverage at a dose of 1 × 10^9^ CFU/d, (3) group administered with *L. reuteri* FN041 solid beverage at a dose of 5 × 10^9^ CFU/d, and (4) group administered with *L. reuteri* FN041 solid beverage at a dose of 1 × 10^10^ CFU/d. Their offspring will be examined for AD development during the 2 years after birth so that the efficacy of maternal use of *L. reuteri* FN041 in the prevention of AD can be analyzed by calculating the cumulative incidence of AD in infants. Adverse reactions will be also recorded. Studies have reported that the most efficient dosage of *L. reuteri* FN041 can be determined within 6 months after birth, as infantile AD often develops in early life and peaks in the third month of life (Guo et al., 2019).

In the second stage of *L. reuteri* FN041 promotion and application, a multicenter cohort study in an expanded research population will be conducted. A total of 500 pregnant females with babies at a high risk for AD will be recruited from four tertiary hospitals: Wuxi Maternity and Child Health Care Hospital affiliated with Jiangnan University, Affiliated Hospital of Qingdao University, Suzhou Municipal Hospital, and Changzhou Maternal and Child Health Hospital. These subjects will be administered with *L. reuteri* FN041 at the optimal dosage determined in the first stage during late pregnancy and lactation; subsequently, their babies will be followed up for AD development for 2 years after birth.

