## Methods

### Eligibility criteria

According to the World Allergy Organization guidelines, a child may be considered at high risk for allergy if a biological parent or sibling has a history of allergic rhinitis, asthma, eczema, or food allergy (Fiocchi et al., 2015). The recruited pregnant females with babies at high risk for AD must meet the following inclusion criteria: healthy pregnant female (14–16 weeks of gestation), the mother or father of the fetus, or previous child of the couple diagnosed with any of the allergic diseases, including asthma, eczema, food allergy, or allergic rhinitis. This information will be confirmed by specific recruiters prior to recruitment. The risk of developing AD in infants without a family history of allergies is approximately 27%, whereas that in infants with one or two parents with an atopic history increases to 37.9 and 50.0%, respectively (Böhme et al., 2003). The population we aim to recruit meets the recommended probiotic target audience according to the guidelines of the World Allergy Organization (Fiocchi et al., 2015). The exclusion criteria are as follows: pregnant female under 16 years of age, multiple pregnancies, known fetal abnormalities, oral administration of immunosuppressive drugs or antibiotics, heart valve disease or immunodeficiency, undergoing dental surgery under antibiotic prevention, history of transplantation or HIV, long-term continuous use or ongoing use or intent to use probiotics before admission, external fertilization pregnancy, previous participation in research, deemed unsuitable for inclusion in the study owing to other medical reasons, and gestational diabetes.

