### Sample size calculation

The cumulative incidence of AD in high-risk infants at 1 and 2 years of age is reported to be approximately 40.1 and 41%, respectively, based on previous studies conducted in other countries (Rautava et al., 2012; Chaoimh et al., 2023). According to a previous study carried out in 2022 in our hospital, the overall point prevalence of AD in infants aged 0–24 months was 50.5% in Wuxi (Ding Y. et al., 2022). The expected cumulative incidence of AD after *L. reuteri* administration is approximately 20%, with a relative 20% reduction in AD incidence of 40% through intervention. Assuming that the first type of error would be 2.5% and the efficacy would be 80%, we calculated the sample using online tools.^1^ The sample size in each group would be 74. Considering a 10% dropout rate, each group should recruit 85 research subjects in the first stage. In the second stage of the trial, the sample size is expected to be approximately 500, which is considered sufficient to further verify the efficacy of maternal use of *L. reuteri* FN041 in the prevention of infantile AD.

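### The stated balancing list for stage 1 names neither hospital nor number of atopic parents; stratifying on both and analysing by those strata is a cheap improvement with a small gain

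*Protocol article*

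**What the plan says.** In Trial design, stage 1 enrols 340 women "recruited from the Wuxi Maternity and Child Health Care Hospital affiliated with Jiangnan University and the Affiliated Hospital of Qingdao University". It adds: "These subjects will be randomly divided into four groups", with 85 in each.

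Allocation and blinding states what the random grouping should achieve: it is done "so that they are consistent with each group according to their age, economic situation, educational level, and other influencing factors". The section gives no stratification factor, block structure or other method.

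Eligibility criteria admits a woman if "the mother or father of the fetus, or previous child of the couple diagnosed with any of the allergic diseases", so couples with two, one or no atopic parent can all enter. The same section puts the risk without a family history at about 27% and says that the risk "in infants with one or two parents with an atopic history increases to 37.9 and 50.0%, respectively".

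Sample size calculation plans for 40% incidence without and 20% with the intervention, and reports that "the overall point prevalence of AD in infants aged 0–24 months was 50.5% in Wuxi". It gives no rate for Qingdao.

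Statistical methods names the chi-squared test for categorical variables and mentions no adjustment. Data collection and sample collection says that family history and other potential confounders are recorded.

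**The concern.** The article lists the factors on which the groups should agree, but the three it names carry no AD risk figure anywhere in the text. Parental atopy carries one and is not named. Hospital is not named either, although a two-site trial is ordinarily stratified by site. The closing catch-all may be meant to cover both, but a randomisation schedule cannot be generated or audited from an open list.

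At stake is chance imbalance between arms in a known risk factor. It would enter each dose-placebo difference and the comparison of doses that decides what goes into stage 2, and the one test that the article names for categorical data would not adjust for it.

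**Working it through.** **Inputs from the article.** Arm size: 340 / 4 = 85. Target difference: 40% − 20% = 20 points. Parental-atopy gap: 50.0 − 37.9 = 12.1 points.

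**Assumptions, because the article gives no figure.** Share of two-parent families: 10% to 50%. Hospitals: equal recruitment, with a gap in AD rate of 10 to 20 points.

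**Step 1: chance imbalance between two arms.** For a factor with share π and n = 85 per arm under simple randomisation, SD = √(2π(1−π)/n), and the 95% limit is 1.96 × SD. The resulting shift in the AD difference is that limit times the risk gap.

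| Share with two atopic parents | SD of imbalance | 95% limit | Shift at a 12.1-point gap |
|---|---|---|---|
| 10% | 4.6 points | 9.0 points | 1.1 points |
| 20% | 6.1 points | 12.0 points | 1.5 points |
| 30% | 7.0 points | 13.8 points | 1.7 points |
| 50% | 7.7 points | 15.0 points | 1.8 points |

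A 15-point imbalance therefore costs 0.15 × 12.1 = 1.8 points, and 15 points is roughly the 95% limit at an even split. With three dose-placebo contrasts, the simulated chance (200,000 allocations) that at least one is out by more than 15 points is about 14% for a 50% factor and 9% for a 30% factor.

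**Step 2: wider gaps.** The widest gap that the article's figures allow is no family history against two atopic parents: 50 − 27 = 23 points. At an even split this gives 0.150 × 23 = 3.5 points. It is an upper bound, because every eligible family has some allergic history. For hospital, the assumed gaps give 0.150 × 10 = 1.5 points and 0.150 × 20 = 3.0 points.

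**Step 3: size relative to sampling error.** The standard error of a dose-placebo difference is √((0.40×0.60 + 0.20×0.80)/85) = 6.9 points. For two doses both at 20% it is √(2×0.20×0.80/85) = 6.1 points. A shift of 1.8 points is thus about 0.26 and 0.30 standard errors.

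**Step 4: power.** Simulation at 74 per arm (the planned number before dropout), halving the risk and using the unadjusted chi-squared test, compared simple randomisation with exact balance on parental atopy:

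| Share with two atopic parents | Power, simple | Power, balanced |
|---|---|---|
| 20% | 77.3% | 77.5% |
| 30% | 79.0% | 79.0% |
| 50% | 82.1% | 82.3% |

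Type I error was about 5.3% to 5.6% either way. A second simulation at 85 per arm replaced simple randomisation and chi-squared with stratified allocation and a stratified test. Power rose by about 0 to 1 point for gaps up to 10 points, and by about 1 to 2 points at an assumed 20-point hospital gap.

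**The case against.** The strongest reply is that the sentence states a purpose: women are randomised so that groups come out comparable, and the factors are examples. Random allocation balances unnamed factors in expectation, the catch-all can include hospital and parental atopy, and family history is recorded, so adjustment remains possible. A condensed article may also leave stratifiers and covariates to a fuller document. Most of this stands, and it limits the point to a suggested improvement of a stated method. It does not make the stated list usable as a randomisation specification.

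A reader might infer more, and the documents do not support it:

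- **That these risk factors are uncontrolled or the comparison biased.** Randomisation rules out systematic bias; only chance imbalance remains.
- **That the article shows a hospital gap of about 10 points, by setting the Wuxi 50.5% against the planning 40%.** The first is a point prevalence in Wuxi infants aged 0 to 24 months, and the second is a planning cumulative incidence for high-risk infants. Neither describes Qingdao.
- **That the named factors form a stratification too sparse to work.** The article does not call them strata and gives no levels.
- **That staff could steer assignments.** The article says that grouping is random, that organisers, researchers and participants are not told the intervention, and that a third party makes the products.

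**Conclusion.** The point holds as a modest one. The balancing statement is open-ended and omits site and the one enrolment factor to which the article itself attaches an AD risk gradient. Under simple randomisation, a 95% chance imbalance in parental atopy shifts a difference by 1.1 to 1.8 points for two-parent shares of 10% to 50%, against a 20-point target. For hospital the figure is 1.5 to 3.0 points, and it rests wholly on an assumed gap. The power gain is at most about 2 points. The case for acting is that the change costs little and removes an avoidable source of noise from comparisons that will select a dose; the planned test is not invalid without it.

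**What to change.** Replace the open list with a permuted-block schedule stratified by hospital (Wuxi, Qingdao) and parental atopy (two atopic parents against one, or a sibling only). Both are known at enrolment. This makes four strata averaging 340 / 4 = 85 women. The two-parent strata would be smaller: at an assumed 30% share and equal hospitals, 340 × 0.30 × 0.50 = 51 each, still enough for blocks across four arms. Compare AD incidence with a test stratified by the same factors, such as Cochran-Mantel-Haenszel, in place of the unadjusted chi-squared test.

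Trial status schedules stage 1 recruitment to end in December 2023, so allocation may already be complete. In that case, prespecify hospital and parental atopy as strata or covariates in the primary comparison before the codes are broken. The precision gain is then minimal, and the change serves mainly as protection against chance imbalance.

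The cost is a new randomisation list, or two terms in the analysis. The downside is that age, income and education cease to be named balancing factors; they can be reported as baseline characteristics.

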### Statistical methods

The data obtained in this study can be divided into continuous and categorical variables, which are presented as the mean ± standard deviation or median with interquartile range and frequency with percentage, respectively. Continuous variables will be analyzed for differences among the groups using ANOVA, whereas categorical variables will be analyzed using the chi-squared test. A two-sided *p-*value of <0.05 will be considered statistically significant.

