### Objectives

This study aims to assess the incidence of infantile AD after maternal consumption of *L. reuteri* FN041 during late pregnancy and lactation. The optimum dosage will be determined by analyzing the efficacy of maternal supplementation with different doses of *L. reuteri* FN041 in preventing AD in offspring. Additionally, the secondary objective is to identify the transfer efficiency of *L. reuteri* FN041 from the mother’s gut to breast milk and then to infant’s gut after oral supplementation.

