#### Secondary outcomes

The severity of gastrointestinal and respiratory symptoms will be analyzed as a secondary outcome. Meanwhile, regulatory T cells in umbilical cord blood at birth (*n* = 20 for each group) will be analyzed via flow cytometry and the levels of transforming growth factor-β, interleukin (IL)-10, IL-12, IL-13, IL-4, interferon-γ (IFN-γ), tumor necrosis factor-α, and total IgE will be determined using enzyme-linked immunosorbent assay. Further, colostrum and 42-day mature milk level of transforming growth factor-β and IL-10 will be tested. Moreover, the relative abundance of sIgA-coated *L. reuteri* FN041 will be analyzed in breast milk and infant feces using strain-specific PCR, depending on the genome sequence information. *Lactobacillus* strains will be isolated and determined using 16 s rRNA sequencing, metagenomic sequencing will be performed to analyze *L. reuteri* FN041 (*n* = 10 for each group), and StrainPhlAn3 will be used to analyze the data at the strain level (Walsh et al., 2017).

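### ANOVA is the only test named for continuous outcomes, although the plan foresees skewed data and the FN041 transfer outcome is likely to be mostly non-detect on placebo

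*Protocol article*

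**What the plan says.** In the Protocol article, Statistical methods, continuous data are to be summarised as "mean ± standard deviation or median with interquartile range". The next sentence assigns the test: "Continuous variables will be analyzed for differences among the groups using ANOVA". Categorical variables get the chi-squared test, and significance is two-sided at 0.05. No transformation, rank test or rule for non-detects is named.

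Under Objectives, "the secondary objective is to identify the transfer efficiency of" FN041 from the mother's gut to milk and then to the infant's gut. The Abstract also presents transfer as the secondary outcome. Under Secondary outcomes, the relative abundance of the sIgA-coated strain "will be analyzed in breast milk and infant feces using strain-specific PCR". The same section lists cytokines and total IgE by ELISA and metagenomic sequencing in 10 per group. Under Data collection and sample collection, milk is taken in three windows and infant feces at five times. The section on concomitant care bars mothers and infants from other probiotic products.

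**The concern.** The plan foresees variables that a mean summarises badly, then names only a test of means. For most laboratory variables that is a mild mismatch. For FN041 abundance it is sharper.

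The assay targets one administered strain, and other probiotics are not allowed. The Introduction adds that *L. reuteri* is far more abundant in milk from the region where the strain was isolated than in urbanised areas, and the first-stage hospitals are in Wuxi and Qingdao. Placebo pairs can therefore be expected to be mostly non-detects, with many non-detects in the active arms too. One arm would then have almost no variance and the others a spike at zero with a long right tail, which is far from the equal-variance normal model behind ANOVA.

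At stake is the chance of showing transfer, which the Introduction presents as the key to prevention through the mother.

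**Working it through.** **The plan's own figures.** There is none to reproduce for these outcomes. The only sample-size calculation is for AD incidence. No detection rate, abundance, SD or effect size is given for FN041, and none for the cytokines.

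**Inputs from the protocol.** Four equal groups; two-sided 0.05; 85 per group with 10% dropout, so 85 × 0.9 = 76.5, taken as 77; metagenomics in 10 per group.

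**Inputs assumed.** FN041 is detected in 0% of placebo and 20%, 30% and 40% of the active arms. Detected values are log-normal with log-SD *s* of 1, 1.5 or 2 and the same distribution in each active arm, so the groups differ only through detection.

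**Why the spread matters.** With detection *p* and log-mean 0, the raw mean is p·exp(s²/2) and the variance is p·exp(2s²) − p²·exp(s²). For the top dose (p = 0.4), against a placebo mean and SD of zero:
- s = 1: mean 0.4 × 1.649 = 0.66; variance 0.4 × 7.389 − 0.16 × 2.718 = 2.52; SD 1.59; mean/SD 0.42.
- s = 1.5: mean 0.4 × 3.080 = 1.23; variance 0.4 × 90.02 − 0.16 × 9.488 = 34.5; SD 5.87; mean/SD 0.21.
- s = 2: mean 0.4 × 7.389 = 2.96; variance 0.4 × 2981 − 0.16 × 54.60 = 1184; SD 34.4; mean/SD 0.09.

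The detection difference is the same in all three cases, but the standardised difference in raw means shrinks about fivefold.

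**Simulated power** (2,000 to 4,000 runs per scenario; for the log scale, non-detects set to half the smallest detected value):

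| n per group | log-SD | ANOVA, raw | Kruskal-Wallis | ANOVA, logs | Chi-squared on detection |
|---|---|---|---|---|---|
| 77 | 1 | 97% | 100% | 100% | 100% |
| 77 | 1.5 | 62% | 100% | 100% | 100% |
| 77 | 2 | 30% | 100% | 100% | 100% |
| 10 | 1 | 14% | 36% | 28% | 38% |
| 10 | 1.5 | 8% | 36% | 28% | 39% |
| 10 | 2 | 5% | 36% | 26% | 39% |

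Repeat runs differ by about 1 percentage point (2 for the rank test at n = 10).

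**Other detection rates at n = 77.** With placebo detection of 0–5% and active detection from 10/20/30% up to 50/70/90%, raw ANOVA had 81–100% power at log-SD 1 and 25–57% at log-SD 2, against about 100% for the rank test.

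**False positives.** With equal 5% detection in all groups, raw ANOVA rejected in 0.2–2.8% of runs across n = 10, 20 and 77. It is conservative here, so the harm is lost power.

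**Cytokines and IgE.** These were assumed log-normal, with n = 20 per group and every active arm shifted by one log-SD. Raw ANOVA against Kruskal-Wallis gave 87% v 89% at log-SD 0.3, 79% v 87% at 0.5, 50% v 88% at 1.0 and 21% v 88% at 1.5. The article ties n = 20 to cord-blood regulatory T cells; whether it also covers the cytokines is unclear, so these figures are illustrative.

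**The case against.** The strongest reply is that a condensed article leaves transformations, non-detects and repeated measures to an analysis plan that is not shown. Naming ANOVA does not exclude ANOVA on logs, which restores nearly all the power at 77 per group. The chi-squared test already named for categorical data would serve a detected/not-detected outcome, and the Discussion itself rests the transmission argument on detecting the strain in milk and feces. Only secondary outcomes are touched.

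Much of this stands and limits the size of the point. It does not remove it. The article assigns one test to all continuous variables without qualification, and Secondary outcomes defines the transfer measure as relative abundance, with no detection endpoint. As worded, the transfer outcome goes to ANOVA.

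Three stronger readings are tempting and are not supported:
- A reader might infer that the transfer outcome loses most of its power. That depends on the assumed spread: at 77 per group and log-SD 1, raw ANOVA keeps 97%.
- A reader might apply n = 20 to the transfer outcome. That number is attached to regulatory T cells; the PCR measure carries no such limit.
- A reader might infer inflated false positives from treating repeated milk and stool samples as independent. Nothing says that samples will be pooled, and analysis at each time has no such inflation.

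**Conclusion.** The point holds as a mismatch between the named test and the data that the plan foresees, chiefly for FN041 transfer. At about 77 per group the power lost by raw-scale ANOVA against a rank or detection test runs from about 3 points (97% v 100%) to about 70 points (30% v 100%) as the log-SD goes from 1 to 2. At the metagenomics size of 10 per group, raw ANOVA has about 5–14% against about 36% for the rank test, so no method is well powered there.

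These figures rest on the assumed 0/20/30/40% detection and log-normal levels. Near-zero detection on placebo is itself an inference. What does not depend on the exact values is the direction: in every simulated scenario with a real group difference, raw ANOVA did no better than the rank test. The primary outcome, cumulative AD incidence, is categorical and unaffected. The change is worth making because it is almost free and, if fixed before unblinding, prevents a choice of test guided by the data.

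**What to change.** Replace the single ANOVA sentence, or confirm in the analysis plan, that:
- at each sampling time, FN041 is analysed as detected or not detected (chi-squared or exact test), with Kruskal-Wallis for abundance;
- cytokines and total IgE are analysed on the log scale or by Kruskal-Wallis;
- if sampling times are combined, a mixed model or GEE is used with the mother-infant pair as the unit.

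The cost is analysis wording only, with no extra participants, samples or visits. The downside is that effects are reported as proportions, ratios or rank shifts instead of mean differences.

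### The only test stated for the primary outcome does not control error when three doses are judged against placebo, and it does not match the single contrast that sets the sample size

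*Protocol article*

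**What the plan says.** - **Design and aim.** The Objectives and Trial design sections of the protocol article describe four equal arms (placebo and three doses, 340 women) and an optimum dose to be found by comparing efficacy across doses.
- **Outcome.** Under Primary outcomes, the endpoint is the cumulative incidence of AD within 2 years of delivery, which is yes or no for each infant.
- **Test.** Statistical methods has one sentence for such data, "whereas categorical variables will be analyzed using the chi-squared test", and one threshold: "A two-sided *p-*value of <0.05 will be considered statistically significant". It names no primary contrast and no rule for several comparisons.
- **Size.** Sample size calculation uses one pair of proportions, "approximately 20%, with a relative 20% reduction in AD incidence of 40% through intervention". Its error rates read "Assuming that the first type of error would be 2.5% and the efficacy would be 80" per cent. The result is 74 per group, and after 10% dropout "each group should recruit 85 research subjects in the first stage". It does not say whether the 2.5% is one-sided or an allowance for several doses.

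**The concern.** Three parts of the plan do not fit together. The objective calls for a statement about each dose against placebo. The sample size assumes one such contrast at 2.5%. The analysis section gives a chi-squared test at 5% with no contrast named. A reader cannot tell whether a positive result means that some groups differ or that a given dose beats placebo, nor at what error rate.

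At stake is the credibility of any dose-specific claim from the randomised stage, and the accuracy of the stated 80% power. Stage 2 gives every woman the product and describes no concurrent placebo group, so stage 1 is the only randomised comparison.

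**Working it through.** **Inputs.** From Sample size calculation: 40% versus 20%, 2.5% type I error, 80% power, 74 per group, 10% dropout, 85 recruited. From Statistical methods: two-sided 0.05. From Trial design: four equal arms. Evaluable per arm is 74 as calculated, or 85 × 0.9 = 76.5, taken as 76.

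**1. The plan's own figure.** For two proportions with pooled variance under the null:

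n = [z(1−α/2)·√(2p̄(1−p̄)) + z(0.80)·√(p1(1−p1)+p2(1−p2))]² / (p1−p2)²

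With p1 = 0.40, p2 = 0.20 and p̄ = 0.30, the roots are √0.42 = 0.648 and √0.40 = 0.632.
- 2.5% one-sided (the same as 5% two-sided): (1.960×0.648 + 0.842×0.632)²/0.04 = 81.2, so 82.
- 2.5% two-sided (z = 2.241): 98.5, so 99.

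Neither gives 74. A control rate of 41%, which the same section cites ("at 1 and 2 years of age is reported to be approximately 40.1 and 41%, respectively"), gives 74.3 at 2.5% one-sided. That is close to 74 and suggests one unadjusted contrast at two-sided 5%. The dropout step is fine: 74/0.9 = 82.2, so 83, and 85 covers it. The phrase relative 20% does not describe a fall from 40% to 20%, which is 20 points absolute and 50% relative.

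**2. Error for three dose-placebo tests.** The three z-statistics share one placebo arm, so with equal arms their correlation is 0.5 under the null. Family-wise error = P(max|Z| > c).
- Each at two-sided 0.05 (c = 1.960): 12.5% by normal theory, and 13.4% to 13.5% by simulation at 40% in all arms with 74 per arm. Treated as independent: 1 − 0.95³ = 14.3%.
- The same simulation, counting only doses significantly better than placebo: about 6.7%.
- Each at two-sided 0.025 (c = 2.241): 6.5%. Treated as independent: 1 − 0.975³ = 7.3%.
- If the 2.5% is one-sided, it is two-sided 5% per comparison, and the first line applies.

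**3. The four-group test.** Under the global null it rejects in 5.0% of simulated trials. If it gates pairwise tests at 0.05, some dose-placebo difference is declared in 4.1%. That protection is lost once one dose works. With true rates 40/40/40/20% and 76 per arm, at least one of the two ineffective doses is declared different from placebo in 9.4% of trials. Roughly half of these (9.4/2 = 4.7%) favour the dose.

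**4. Power per dose, 40% versus 20%.** Power = Φ{[0.20·√n − z·0.648]/0.632}.

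| Level per comparison (two-sided) | z | 74 per arm | 76 per arm |
|---|---|---|---|
| 0.05, unadjusted | 1.960 | 76% | 77% |
| 0.0188, Dunnett | 2.349 | 62% | 64% |
| 0.0167, Bonferroni | 2.394 | 61% | 62% |

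Simulation agrees to about one point (77% unadjusted and 61% Bonferroni at 74 per arm). Bonferroni is the floor for Holm, which gains power when more than one dose works.

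**5. Sensitivity.** If the control rate is 41%, power at 74 per arm is 80% unadjusted and 65% at the Bonferroni level. If all 85 per arm were evaluable at 40% versus 20%, the figures would be 82% and 68%.

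**6. Size for 80% per dose after adjustment, 40% versus 20%.** Bonferroni: 109 evaluable, 109/0.9 = 121.1, so 122 recruited per arm and 488 in all. Dunnett: 106 evaluable, 106/0.9 = 117.8, so 118 per arm and 472 in all. The plan has 340.

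**The case against.** **The article does not say it will run pairwise tests at 0.05.** This is true. The methods sentence is generic, and the words about differences among groups are attached to ANOVA. If only the four-group test is run, error under the global null is 5%, and it would be wrong to say that the stated test has a 13% error rate. But that test alone does not meet the objective of judging doses, and the obvious ways of going on to dose-specific claims all exceed 5%.

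**Multiplicity detail belongs in an analysis plan, which is not shown.** The choice between Holm and Dunnett could be left there. The article, however, commits to a test, a level and a power figure. These conflict with its aim and with each other, and the power depends on the level chosen.

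**Stronger readings that the documents do not support:**
- *An ineffective product has a 13% chance of being declared effective.* The 13% counts differences in both directions. A dose falsely better than placebo occurs in about 6.7% of null trials.
- *A false positive at 24 months would carry a dose into stage 2.* Trial design says the dose can be determined within 6 months after birth, and Trial status starts stage 2 recruitment in July 2024. The women in stage 1 were to be recruited from July to December 2023, so the 24-month result cannot gate stage 2. No section makes significance a condition for choosing the dose.
- *The trial is sized for three comparisons.* It is sized on one contrast, applied to every arm.
- *The unadjusted test is invalid because randomisation seeks balance* ("so that they are consistent with each group according to their age, economic situation, educational level, and other influencing factors") *and because parental history moves risk* (it "increases to 37.9 and 50.0%, respectively"). No strata are defined and the unadjusted test stays valid. The gain from adjustment is about 1 point of power at the article's own risk figures with an assumed centre effect. Covariate choice is ordinarily left to the analysis plan.
- *A trend test should replace the four-group test.* It is a trade-off. At 40/35/28/20% the trend test has 81% power against 66%. On a plateau of 40/20/20/20% it has 76% against 81%, and when only the top dose works 69% against 78%.

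**Conclusion.** The point holds as a mismatch between objective, sample size and analysis. The stated test controls error for the question whether any groups differ, but not for the dose-specific conclusions that stage 1 is meant to give. Separate tests at 0.05 have about 13% family-wise two-sided error, or about 6.7% in the favourable direction. Gating on the four-group test leaves about 9% when only one dose works. The 2.5% in the sample size section, read as two-sided per comparison, leaves about 6.5%.

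The stated 80% power is about 61-64% per dose at an adjusted level, and about 77% even without adjustment.

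These figures assume 40% versus 20%, 74 to 76 evaluable infants per arm, equal arms and a shared placebo. The unadjusted shortfall depends on the 40% rate and disappears at 41%. The shortfall after adjustment remains in every case examined.

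**What to change.** Reconcile Sample size calculation with Statistical methods:
1. Name the three dose-placebo contrasts in 2-year cumulative incidence as the primary analysis.
2. State one alpha and its sidedness, and use it in both sections.
3. Control the family-wise two-sided 5% level over the three contrasts with Holm or Dunnett.
4. Replace the 80% with per-dose power at the adjusted level for 74 to 76 evaluable per arm (about 61-64% at 40% versus 20%), and correct the inputs so that the group size can be reproduced.
5. If a dose-response question is wanted, prespecify a trend test as a supplement to these contrasts, not as a replacement.

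This takes a few sentences and no new data. The downside is a visibly lower stated power. Restoring 80% per dose would take 472 to 488 women instead of 340, so with recruitment planned to finish in December 2023 the realistic course is to state the lower power openly.
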